
## 1. Background

Stroke represents a major global health burden, ranking as the second leading cause of mortality and the third leading cause of combined mortality and disability as measured by disability-adjusted life years (DALYs) worldwide [1,2]. In Singapore, the incidence of stroke increased substantially over the last decade. According to data from the Singapore Stroke Registry, there were 9702 stroke episodes in 2022, representing a more than 50% increase compared with 6367 episodes reported in 2012 [3]. This rise reflects a growing stroke burden in the nation [4]. Among the multiple consequences of stroke, upper limb impairments are particularly prevalent and debilitating, with approximately 70% of stroke survivors demonstrating altered arm function, 40% maintaining persistent functional disability, and only 5–20% achieving complete dexterity recovery at 6 months post-stroke [5,6].

Current rehabilitation options for stroke-related UL impairment include conventional occupational therapy (OT), constraint-induced movement therapy (CIMT), robot-assisted therapy (RAT), and non-invasive brain stimulation techniques such as transcranial magnetic stimulation (TMS) and transcranial direct current stimulation (tDCS) [7,8,9]. Conventional OT remains the cornerstone of standard post-stroke arm and hand rehabilitation, focusing on task-specific training and activities of daily living retraining; however, its benefits are contingent on the patient’s capacity for active voluntary movement, limiting its utility in patients with severe motor deficits. CIMT, which involves intensive use of the paretic limb with restraint of the unaffected limb, has demonstrated meaningful and enduring efficacy in patients with at least some residual distal motor function but is poorly tolerated in the acute setting, requires strict inclusion criteria and patient selection, and is unsuitable for patients with complete plegia [7]. RAT offers the advantage of delivering high-repetition, task-specific training with reduced therapist burden possible through minimally supervised care models, but widespread access is often limited by prohibitive cost and complexity of devices, inconsistent adoption related to cost-effectiveness data, and organizational factors impacting intensive service delivery mimicking research protocols [8]. Non-invasive brain stimulation serves as a promising adjunct by modulating cortical excitability; however, functional recovery is modest and heterogeneous across trials, with uncertain durability [9]. All conventional approaches lack a direct, real-time link between a patient’s motor intention and the resulting limb movement, limiting Hebbian-based neuroplastic changes, particularly in patients with severe corticospinal tract disruption [10].

Brain–computer interface (BCI) addresses this lack of a closed-loop system connecting volitional intent with limb movement [11,12]. BCI records neural signals, decodes motor intents, and uses decoded signals to control either external devices (end effector robots or neuroprostheses or virtual reality (VR platforms), or internal effectors (functional electrical stimulation of the patient’s muscles [13,14], thus reestablishing volitional control of their paretic limbs through motor imagery via electroencephalographic (EEG) signal decoding or MI-EEG feedback [15] and restoring temporal dependence between cortical (presynaptic) and end effector (postsynaptic) neurons. The resulting successful MI-EEG triggering the end-effector limb movement in turn generates ascending sensory perception, completing a closed-loop biofeedback system that reinforces motor learning [16,17].

Recent systematic reviews and meta-analyses have demonstrated that BCI-based rehabilitation produces clinically and statistically significant improvements in upper extremity motor function [18,19,20]. Locally, Ang et al. (2011) conducted a large clinical study demonstrating that stroke patients could successfully use EEG-based motor imagery BCI, establishing feasibility in this population [21]. Subsequent research by Várkuti et al. (2013) showed that resting state changes in functional connectivity correlated with movement recovery following BCI and robot-assisted upper-extremity training [22]. Ang et al. (2015) in two randomized controlled trials comparing duration-matched controls with either RAT or BCI-RAT paired with either shoulder–hand or wrist–hand end-effector robots, demonstrated the efficacy of MI-EEG-RAT in chronic stroke patients with significant pre/post-training effects without significant inter-group differences between conventional UE rehabilitation controls, robotic only, and BCI-RAT intervention groups [21,23]. Furthermore, BCI-RAT groups were associated with high levels of safety, and within group impairment reductions were sustained till week 24 follow-up, thus providing an important foundation for extending BCI research into the subacute/chronic stroke inpatient populations [21,23].

Existing studies, however, involved predominantly chronic stroke patients. In our recent meta-analysis of predominantly chronic stroke cohorts, BCI rehabilitation produced a mean improvement of 5.23 points on the Fugl–Meyer Assessment Upper Extremity (95% confidence interval 3.85 to 6.61; total score range 0 to 66, with higher scores indicating less impairment), exceeding the established minimal clinically important difference of 4 to 6 points for the FMA-UE [24]. We hypothesize that there may potentially be greater benefits when BCI is applied during the acute/subacute phase when neuroplasticity is heightened. Notably, an overview of systematic reviews by Liu et al. (2025) concluded that BCI-combined treatment improves upper limb motor function and quality of daily life, with effects particularly pronounced in the subacute phase [25]. In acute and subacute stroke, several studies have alluded to moderate quality evidence and high safety profile and efficacy of BCI when coupled with end effectors such as FES, VR, or robots, achieving mean FMA-UE difference of 3.69–5.02 albeit with less robust gains for ADL independence. Subgroup analyses indicated that interventions < 30 days of stroke for <3 weeks may yield greater benefits, in particular paired with FES. Optimal training parameters suggested daily sessions of 20–90 min or 2–5 times weekly for 3–4 weeks [26,27] (Figure 1).

However, practical implementation of BCI technology within acute inpatient hospital settings presents logistical challenges and must also be carefully evaluated. The setup of EEG headsets with wet electrodes requires trained personnel and can add at least 10–15 min of preparation time per session, including set-down and scalp cleansing after MI-BCI to achieve adequate electrode impedance [28,29].

Lastly, economic data remain scarce, creating barriers to widespread implementation in healthcare systems [30]. Understanding the incremental cost-effectiveness of BCI rehabilitation compared to standard care is essential for informing policy decisions regarding technology adoption and reimbursement. This study therefore incorporates a prospective economic evaluation alongside the clinical feasibility assessment to generate preliminary cost-effectiveness evidence.

This protocol addresses three gaps that, to our knowledge, have not previously been examined together in the BCI stroke rehabilitation literature. First, almost all existing BCI evidence is derived from chronic stroke survivors who have already plateaued after conventional rehabilitation, whereas the acute and early subacute inpatient phase, when neuroplasticity is theoretically greatest, remains largely untested. This phase also presents distinct patient selection challenges because reduced attention, fatigability, and medical instability are common early after stroke and may constrain who can engage with an attention-dependent motor imagery paradigm; this consideration directly informs our cognitive and tolerance-based eligibility criteria. Second, no existing study has evaluated the translation of BCI into routine ward practice through an implementation science lens despite well-recognized barriers relating to electrode set-up time, staffing, and device complexity. Third, no prior BCI rehabilitation study has reported a preliminary health economic evaluation, leaving decision-makers without cost-effectiveness evidence to guide adoption. In addition, the acute and severe stroke population has a particular need for, yet limited published safety data exist on, closed-loop BCI; systematic capture of adverse events such as fatigue, skin reactions, and seizure risk in this more vulnerable group is therefore a deliberate focus of this study.

The aims of this study protocol are to (1) establish the feasibility, usability, and safety of implementing BCI-based rehabilitation during the inpatient acute/early subacute stroke phase; (2) evaluate clinical efficacy outcomes with regards to motor impairment scales and quality of life measures; (3) characterize the electrophysiological correlates of motor recovery during this critical neuroplasticity window; and (4) conduct preliminary health economic evaluation.

## 2. Methods

### 2.1. Study Design

This is a prospective, open-label, single-arm pragmatic feasibility pilot trial employing consecutive sampling with independent and periodic outcome assessments, incorporating a preliminary cost analysis using historical controls. A CONSORT-compliant participant flow diagram will be included in the results publication. The study has been designed following the Standard Protocol Items: Recommendations for Interventional Trials (SPIRIT) guidelines and will be reported according to Consolidated Standards of Reporting Trials (CONSORT) extension for pilot and feasibility trials [31,32]. The economic evaluation will follow the Consolidated Health Economic Evaluation Reporting Standard (CHEERS) guidelines [33].

### 2.2. Study Setting

Participants will be recruited from the inpatient rehabilitation unit of Tan Tock Seng Hospital (TTSH)-Integrated Care Hub (TTSH-ICH), which receives referrals from the acute stroke units of National Neuroscience Institute (NNI), Singapore.

### 2.3. Eligibility Criteria

**Inclusion criteria are as follows:** adults aged 21–80 years with confirmed hemorrhagic or ischemic stroke on neuroimaging, stroke onset within 2–12 weeks; demonstrated voluntary finger flexion or extension by Oxford Medical Research Council (MRC) grade 0–4/5, Montreal Cognitive Assessment (MoCA) score > 20/30; ability to understand written and spoken instructions; and stable medical and neurological status as determined by the clinical team [34]. Because the closed-loop paradigm depends on integrating afferent (proprioceptive and visual) feedback with efferent motor intent, lesion location will be documented from neuroimaging; participants with predominantly cerebellar or brainstem lesions—who may retain intact primary sensation yet have impaired updating of internal sensorimotor (forward) models, that is, impaired predictive coding—will remain eligible but will be flagged a priori. For such participants the intervention explicitly leverages the multimodal, error-corrective feedback intrinsic to the recoveriX loop (synchronized FES-evoked movement together with visual avatar feedback) as an externally supplied source of sensory prediction; their decoding performance and clinical response will be examined as an exploratory subgroup to determine whether impaired predictive coding attenuates BCI benefit and should inform eligibility for a future definitive trial. Because the motor-imagery-related event-related desynchronization (ERD) used for BCI classification is recorded over central sensorimotor electrodes (FC3–CP4) rather than posterior/occipital sites, cerebellar lesions are not expected to directly impair this signal; ERD magnitude and BCI performance in this subgroup will nonetheless be examined exploratively as above.

**Exclusion criteria are as follows:** previous diagnosis of stroke; implanted pacemaker or continuous infusion pump; history of seizures or epilepsy; previous neurosurgical procedures, medical instability as determined by the study team; severe blindness; anticipated life expectancy less than 6 months; hemodialysis requirement; inability to follow one-step commands; severe aphasia or dysarthria; severe arm/hand pain (Visual Analog Scale > 4/10); severe hemianesthesia or spasticity in the paretic arm (Modified Ashworth Scale greater than 2, out of 4); fixed shoulder or finger joint contractures; active arthritis in any upper limb joint; inability to tolerate upright supported sitting for at least 45 min; and disorders of consciousness or altered arousal states precluding active participation.

Written informed consent will be obtained from all participants or their legally appointed representatives, the latter group applicable to those with MoCA 21–25/30.

### 2.4. Sample Size

Based on comparable feasibility studies in BCI stroke rehabilitation literature and recommendations from our recent meta-analysis [24], a sample of 10 subjects will be sufficient for this feasibility study. Accounting for a 20% dropout rate (*n* = 2), the final proposed sample size is 12 participants. Recruitment will aim to stratify the sample by stroke type in an approximate ratio of 40% hemorrhagic (ICH) to 60% ischemic (infarct) stroke, consistent with local case-mix.

This sample size follows established guidance for pilot and feasibility trials, in which the objective is to estimate feasibility parameters and their variability rather than to test efficacy; widely cited recommendations propose approximately 12 participants for pilot studies [35,36], and a sample of 10–12 is adequate to estimate a feasibility proportion of about 80% (for example recruitment or adherence) with a 95% confidence interval half-width of roughly ±20%. A formal efficacy-based power calculation is therefore not appropriate for the present feasibility endpoints. Nonetheless, to inform the design of a future definitive trial, an indicative a priori power calculation was performed in G*Power (version 3.1). Anchoring conservatively on 6 points—the lower end of the FMA-UE minimal clinically important difference range established largely in chronic stroke (4–6 points)—acute-stroke-specific estimates are reportedly higher, approximately 7–10 points, but 6 points was retained as a conservative estimate and the pooled effect implied by our meta-analysis (mean change 5.23 points, standard error 0.70; approximate standard deviation 3.4 in the analyzed cohorts) [24]; a two-sided paired within-group comparison (α = 0.05, power = 0.80) would require approximately 6–8 participants to detect a change of the minimal clinically important difference magnitude, whereas a two-arm parallel comparison designed to detect a 4-point between-group difference at an assumed standard deviation of 6 (Cohen’s d ≈ 0.67) would require approximately 37–46 participants per arm. The variance and recruitment-rate estimates generated by the present feasibility study will be used to refine these calculations and to power the subsequent randomized controlled trial.

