### 2.5. Study Hypotheses

This feasibility pilot trial will test the following primary hypotheses:

1. Usability: Mean System Usability Scale (SUS) score > 70 in 75% [9] of participants.

2. Session adherence: 75% [9] of participants completing > 24 min (>80%) of each scheduled 30 min BCI session.

3. Program completion: >75% [9] of enrolled participants completing 80% planned sessions (12/15). Commencement of occupational therapy sessions within 30–60 min of completion of MI-EEG. Inpatient drop out < 20% (<3) excluding unanticipated medical/neurosurgical reasons or unplanned early discharge. Participants who are unexpectedly discharged early or become medically unwell will be recorded as protocol deviations and reasons documented.

4. Safety: Training-related adverse events per total delivered sessions ≤ 17% (≤2/12 sessions). These are described as headache or pain from cap or FES application by visual analogue scale (VAS > 5/10, skin changes (from cap or FES electrodes, blurring of vision, from computer eye fatigue, seizures, mental fatigue).

Secondary hypotheses include the following:

(i) Clinical efficacy and post-stroke dependency measured by FMA-UE, ARAT, FIM, MBI.

(ii) Health-related quality of life by SIS-3.0 (arm, hand, activities of daily living-ADL, societal participation, global rating of recovery, domains 1, 5, 7, 8, 9).

(iii) Preliminary cost-effectiveness estimates stratified by baseline severity, including program cost comparisons and the incremental cost-effectiveness ratio (ICER).

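### Section 2.4 takes the 20% dropout allowance on 10 evaluable participants instead of on the 12 enrolled, so 12 enrolled covers 16.7% dropout, not 20% (minor)

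*Protocol article*

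**What the plan says.** The sample-size argument in section 2.4 starts from a target: "a sample of 10 subjects will be sufficient for this feasibility study". It then adds the allowance: "Accounting for a 20% dropout rate (*n* = 2), the final proposed sample size is 12 participants".

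The same section supports the size in two further ways. It cites outside guidance, "widely cited recommendations propose approximately 12 participants for pilot studies", and it gives a precision argument, "a sample of 10–12 is adequate to estimate a feasibility proportion of about 80" per cent, with a 95% confidence half-width of roughly 20 points. It adds that the variance and recruitment estimates from this study will be used to power the later randomized trial.

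Section 2.5 uses 20% again, as a benchmark: "Inpatient drop out < 20% (<3) excluding unanticipated medical/neurosurgical reasons or unplanned early discharge". It counts program completion as a share "of enrolled participants completing 80% planned sessions (12/15"), that is, over everyone enrolled.

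**The concern.** A dropout rate is a share of the people who enter a study. Section 2.4 applies its rate to the people who should be left at the end. The sentence therefore tells the reader that 12 enrolled absorbs 20% dropout and leaves 10, and it does not.

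Section 2.5 uses the enrolled base. With 12 enrolled, 20% is 2.4, so a rate under 20% means at most 2 dropouts, which matches the printed limit of fewer than 3. On a base of 10, under 20% would mean at most 1. Two losses are thus the full 20% in section 2.4 and less than 20% in section 2.5.

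What is at stake is the number of participants with post-baseline data. The FMA-UE change to week 3–4 is the principal clinical anchor for the biomarker analyses (section 3.1), the within-subject comparisons use the Wilcoxon signed-rank test (section 3.12), and the variance estimate feeds the next sample-size calculation (section 2.4). All of these rest on participants who were assessed again, not on all 12 enrolled.

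**Working it through.** **Inputs, all from section 2.4:** evaluable target 10; dropout rate 20%; allowance 2; proposed enrolment 12.

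**1. The plan's own figure.** 10 × (1 + 0.20) = 12, with an allowance of 10 × 0.20 = 2. This reproduces both printed numbers and shows that the base used is 10.

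**2. The same rate on those enrolled.**
- Expected completers from 12: 12 × (1 − 0.20) = 9.6.
- Dropout rate at which 12 leaves 10: 2/12 = 16.7%.
- Enrolment that holds 10 in expectation at 20%: 10/(1 − 0.20) = 12.5, rounded up to 13, with 13 × 0.8 = 10.4 expected completers.

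**3. Chance of ending below 10.** Assume independent dropout with probability 0.20, so that completers follow a binomial distribution.
- 12 enrolled: P(X ≥ 10) = 66 × 0.8¹⁰ × 0.2² + 12 × 0.8¹¹ × 0.2 + 0.8¹² = 0.2835 + 0.2062 + 0.0687 = 0.558. P(X < 10) = 0.442.
- 13 enrolled: P(X ≥ 10) = 286 × 0.8¹⁰ × 0.2³ + 78 × 0.8¹¹ × 0.2² + 13 × 0.8¹² × 0.2 + 0.8¹³ = 0.2457 + 0.2680 + 0.1787 + 0.0550 = 0.747. P(X < 10) = 0.253.
- Difference due to the base: 44.2% − 25.3% = 18.9 percentage points. The other 25 points are ordinary binomial variation, which remains when enrolment is inflated to meet the target only on average.

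**4. Dependence on the rate, P(X < 10):**

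| True dropout | 12 enrolled | 13 enrolled |
|---|---|---|
| 10% | 11% | 3% |
| 15% | 26% | 12% |
| 16.7% | 32% | 16% |
| 20% | 44% | 25% |
| 25% | 61% | 42% |

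**5. Effect on precision, in expectation.**
- Wald half-width for a proportion of 0.8, 1.96 × √(0.8 × 0.2/n): 24.8 points at n = 10 and 25.3 at n = 9.6.
- Approximate relative standard error of a standard deviation, 1/√(2(n − 1)): 23.6% at n = 10 and 24.1% at n = 9.6.

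The average loss of precision is about half a percentage point on either measure.

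**The case against.** The strongest reply is that nothing in the design depends on this step.

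- **The arithmetic is open and reproducible.** The section prints 10, 20%, 2 and 12, so the base can be seen. This stands: the fault is the choice of denominator, and it would be wrong to say that the printed rate cannot give the printed N.
- **Ten is not a requirement.** A reader might infer that the trial fails if fewer than 10 complete. The document calls 10 sufficient, sets no threshold on completers, and says that a formal efficacy-based power calculation is not appropriate for its feasibility endpoints. This stands.
- **Twelve has other support.** The pilot guidance and the 10–12 range would justify 12 even with the dropout sentence removed. This stands, and it is why the sample size need not change.
- **The 44% is not the price of the error.** A reader might attribute all of it to the base. With 13 enrolled, 25% would remain, and the figure moves widely with the assumed rate. This stands.
- **Feasibility rates keep their denominators.** A reader might infer that all the rates used to plan the next trial rest on completers. Program completion is counted over those enrolled and the recruitment rate over those screened (Abstract), so the documents do not support that.
- **The dropout benchmark already implies at least 10 of 12.** This stands only in part. The benchmark in section 2.5 leaves out medical and neurosurgical reasons and unplanned early discharge. Such losses can also cost outcome data, and section 1 describes medical instability as common early after stroke.

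After all this, one sentence in section 2.4 still states that 12 covers a dropout rate it does not cover.

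**Conclusion.** The point holds as a minor arithmetic correction. At the stated 20% dropout, 12 enrolled give 9.6 expected completers, 0.4 short of the number that section 2.4 calls sufficient; 10 completers corresponds to 16.7% dropout. The chance of fewer than 10 is about 44% with 12 enrolled against 25% with 13, so the base accounts for about 19 percentage points of it.

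The expected values follow from the printed inputs alone. The probabilities also assume independent dropout at exactly 20%, and the consequence for outcomes assumes that a dropout contributes no post-baseline data. The consequence is confined to post-baseline outcomes such as the FMA-UE change and its variance. The documents do not support the stronger conclusions that 12 is an inadequate sample or that the feasibility assessment is compromised.

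**What to change.** Keep N = 12 and reword the dropout sentence in section 2.4 in one of two ways:

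- 12 enrolled allows for about 17% dropout (2 of 12) and leaves 10; or
- at 20% dropout, 12 enrolled leaves about 9–10 completers (expected 9.6).

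Either wording puts section 2.4 on the enrolled base that the dropout benchmark in section 2.5 already uses. The cost is one sentence: no extra participants and no change to endpoints or analyses. The stated retention simply becomes slightly less favourable.

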### 2.5. Study Hypotheses

This feasibility pilot trial will test the following primary hypotheses:

1. Usability: Mean System Usability Scale (SUS) score > 70 in 75% [9] of participants.

2. Session adherence: 75% [9] of participants completing > 24 min (>80%) of each scheduled 30 min BCI session.

3. Program completion: >75% [9] of enrolled participants completing 80% planned sessions (12/15). Commencement of occupational therapy sessions within 30–60 min of completion of MI-EEG. Inpatient drop out < 20% (<3) excluding unanticipated medical/neurosurgical reasons or unplanned early discharge. Participants who are unexpectedly discharged early or become medically unwell will be recorded as protocol deviations and reasons documented.

4. Safety: Training-related adverse events per total delivered sessions ≤ 17% (≤2/12 sessions). These are described as headache or pain from cap or FES application by visual analogue scale (VAS > 5/10, skin changes (from cap or FES electrodes, blurring of vision, from computer eye fatigue, seizures, mental fatigue).

Secondary hypotheses include the following:

(i) Clinical efficacy and post-stroke dependency measured by FMA-UE, ARAT, FIM, MBI.

(ii) Health-related quality of life by SIS-3.0 (arm, hand, activities of daily living-ADL, societal participation, global rating of recovery, domains 1, 5, 7, 8, 9).

(iii) Preliminary cost-effectiveness estimates stratified by baseline severity, including program cost comparisons and the incremental cost-effectiveness ratio (ICER).

